### 2.10. Feasibility and Acceptability Assessment

Feasibility will be assessed using indicators such as recruitment rate, session attendance, retention rate, and adherence to the intervention protocol. Acceptability will be evaluated through a brief post-intervention questionnaire consisting of open-ended questions addressing participants’ satisfaction, perceived usefulness, and overall experience with the program.

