However, there are no previous studies that have analyzed the effects of a multidomain program on healthy middle-aged and older adults with interventions of less than one year, which could help make implementation more feasible and reduce drop-out rates [25]. Furthermore, no previous research has examined the effects of a multidomain intervention conducted outdoors, even though outdoor exercise interventions are expected to become pivotal in interventions to improve the health of older people [26].

Consequently, the aim of this protocol is to conduct a preliminary study that explores the effects of an 18-week, twice-weekly outdoor multidomain intervention—including physical exercise, cognitive stimulation, and social engagement—on the health of late middle-aged and older adults. This study also seeks to assess the feasibility and acceptability of the intervention, thereby informing the design of future large-scale trials by evaluating both its potential effects and feasibility. Additionally, this study aims to assess the feasibility and acceptability of the ACTIVA intervention among older adults, to inform future larger-scale trials. We hypothesize that the ACTIVA-Senior program, conducted entirely in an open-air environment, will lead to significant improvements in cognitive, physical, and psychological outcomes. Moreover, the outdoor setting may contribute to greater adherence, enhanced social interaction, and a more enjoyable and relaxed experience, potentially amplifying the overall impact of the intervention on the participants.

This protocol describes a single-blind randomized controlled trial designed as a preliminary and exploratory study. Its dual aim is to evaluate the feasibility and acceptability of an outdoor multidomain intervention for late middle-aged and older adults and to examine its initial effects on cognitive, physical, and psychological health outcomes.

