### 2.4. Participant Recruitment

Although baseline assessments and the intervention have not yet commenced, participant recruitment and randomization have already been completed. A convenience sampling method was employed to recruit middle-aged and older adults through direct communication and email outreach within the senior university program at the University of Almeria. All potential participants were contacted individually.

To be included in the study, participants were expected to meet the following criteria: (a) aged 55 or over; (b) being physically independent; (c) being enrolled in the university for seniors’ program; and (d) passing a medical examination prior to participation, including an electrocardiogram (EKG) under stress conditions. The exclusion criteria were: (a) engaging in moderate or vigorous cardiovascular exercise systematically (≥150 min per week); (b) performing strength training systematically in the last 2 months; (c) having a body mass index (BMI) greater than 35 kg/m^2^; (d) diagnosed with ischemic heart disease, severe aortic stenosis, uncontrolled arrhythmias, decompensated heart failure, acute myocarditis, severe peripheral arterial disease, cerebrovascular accident, thromboembolic disease, aortic aneurysm, clinically significant renal or hepatic failure, severe chronic obstructive pulmonary disease (COPD), clinically significant acute infections, severe psychiatric illness, uncontrolled metabolic diseases, musculoskeletal pathologies, or osteoporosis; (e) uncontrolled blood pressure (systolic blood pressure > 180 mmHg and diastolic blood pressure > 110 mmHg); (f) other pathologies contraindicating physical exercise, identified through the mandatory medical examination that all participants underwent; (g) participants not attending both of the assessments; and (h) participants of the TG who do not attend at least 75% of the sessions (Figure 1).

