### 2.6. Intervention

The TG will follow an outdoor multidomain training program in groups of no more than six participants. All sessions will take place in an open-air facility, equipped with sports equipment such as dumbbells, kettlebells, plyometric boxes, sandbags, resistance bands, and other functional training materials. Although cognitive training is a structured component of the intervention, activities related to emotional intelligence will be incorporated separately through playful, interactive, and socially engaging tasks. These will be intended to support emotional and relational well-being and are evaluated as an independent exploratory outcome.

The outdoor multidomain training program will include resistance training, cardiorespiratory, balance, coordination, flexibility, relaxation, playful and relational tasks related to emotional intelligence, and cognitive training. The program will be based on the HEALTHY-AGE multidomain intervention [45], and it is designed for middle-aged and older people, with the weekly distribution of session content detailed in Table 2. The program will have a duration of 18 weeks of training, with a frequency of two days per week and a duration of 60 min per session conducted face-to-face. The training sessions will be divided into three parts and will include the following components: (1) warm-up (10 min): activation exercises and joint mobility exercises; (2) main part (40 min): resistance training, cardiorespiratory training, and balance and coordination; and (3) cool-down (10 min): flexibility, relaxation, and playful and relational tasks related to emotional intelligence. Cognitive tasks will be integrated in a cross-cutting manner in all parts of the session.

The cognitive component will progressively increase in complexity across the 18-week period, beginning with basic sensorimotor and attention tasks, and gradually incorporating dual-task challenges, memory recall, and executive function elements. Trainers will be guided by a structured progression plan to ensure appropriate cognitive load and adaptation for each participant. Adherence will be monitored daily using electronic forms completed by the trainers. Attendance will be recorded for each session, along with an evaluation of each participant’s performance based on session objectives, exercise intensity, volume, and overall engagement.

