## Figures and Tables

**Figure 1 healthcare-13-01110-f001:**
[figure not shown]
Consolidated Standards of Reporting Trials flow diagram showing the flow of participants through each stage of the study. NOTE: The follow-up accounts for potential participant exclusion based on expected attrition observed in previous studies.

**Table 1 healthcare-13-01110-t001:** SPIRIT schedule of enrolment, interventions, and assessments.

Study Period	Enrolment	Pre-Intervention (Pre-Test)	Familiarization (2 Weeks)	Intervention (Weeks 1–18)	Post-Intervention (Post-Test)	3-Month Follow-Up (Re-Test 1)	6-Month Follow-Up (Re-Test 2)
Informed Consent	X						
Eligibility Screening	X						
Randomization	X						
Baseline Assessments		X					
Multidomain Intervention			X	X			
Outcome Assessments					X	X	X

**Table 2 healthcare-13-01110-t002:** Distribution of content between the weekly sessions.

Session Part	Content	Details	Monitoring	Cognitive Integration
Warm-up (10 min)	- Activation exercises - Joint mobility	Playful tasks and movement prep activities; progressive cardiorespiratory stimulus.	RPE (Borg), trainer supervision	Sensorimotor activities, coordination-based games
Main (40 min)	First weekly session Local muscle endurance (1) Balance and coordination	Circuit of 8 exercises (6 strength, 2 balance/coordination). 3–4 sets of 10–12 reps. 20–30 s rest between exercises. Equipment: dumbbells, bands, TRX.	OMNI-RES RPE (6–7/10), trainer diary	Dual tasks (e.g., movement + verbal/cognitive tasks)
	Second weekly session Power training + local muscle endurance (2) Cardiorespiratory	Power block: 3 exercises, 2 sets of 6–8 reps. Load moved as fast as possible. Local muscle endurance block: 3 exercises, 3 sets of 10–12 reps. Cardio: 2 × 4 min intervals, moderate to vigorous using the talk test.	OMNI-RES RPE, Borg scale, trainer diary	Dual tasks, attention/memory components
Cool-down (10 min)	- Flexibility - Relaxation - Emotional intelligence tasks	Static stretching (8 exercises, 10–30 s), body–mind exercises (Tai Chi, breathing), emotional intelligence games (collaboration, expression of feelings).	Trainer checklist	Breathing visualization, reflective and emotional tasks
Autonomous training	Brisk walking (2×/week)	30+ min per session, moderate intensity. Monitored via self-reported training diaries and talk test.	Training diary (duration, distance, RPE)	—

**Table 3 healthcare-13-01110-t003:** Description of outcome measures.

	Dimension	Test	Description

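### If the 75% attendance exclusion in section 2.4 (h) is applied to the feasibility figures, it truncates training-group attendance at 75% and distorts retention in that arm only

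*Protocol article*

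**What the plan says.** All references are to the protocol article.

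- **Section 2.10** names the feasibility indicators: "Feasibility will be assessed using indicators such as recruitment rate, session attendance, retention rate, and adherence to the intervention protocol". It gives no denominator and does not define retention.
- **Section 2.4, criterion (h)** excludes "participants of the TG who do not attend at least 75% of the sessions". Criterion (g) separately excludes "participants not attending both of the assessments", and that one applies to both arms.
- **Section 2.4** also fixes the timing: "Although baseline assessments and the intervention have not yet commenced, participant recruitment and randomization have already been completed".
- **Section 2.6** sets the number of supervised sessions: "The program will have a duration of 18 weeks of training, with a frequency of two days per week". It adds that "Attendance will be recorded for each session, along with an evaluation of each participant’s performance".
- **Section 2.9** declares intention to treat for group comparisons, with adjustment for adherence.
- **The note to Figure 1** reads: "The follow-up accounts for potential participant exclusion based on expected attrition observed in previous studies".
- **The Introduction** makes feasibility one half of a dual aim, with the purpose of "informing the design of future large-scale trials by evaluating both its potential effects and feasibility".

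**The concern.** The same variable is used in two ways. Attendance below 75% is a reason for exclusion from the study, and attendance is also one of the results by which feasibility will be judged. A summary of attendance among people selected for good attendance says little about how well the programme is attended.

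Retention has a related problem. Criteria (g) and (h) are separate, so a training-group member can attend every assessment and still be excluded for missing sessions. A control participant has no sessions to miss. If exclusions are counted as losses, training-group retention mixes leaving the trial with attending too few sessions, while control-group retention measures only the first.

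The designer of the larger trial needs both numbers: attendance to judge whether the programme can be delivered, and retention to set the dropout allowance. This point concerns those feasibility figures, not the comparison of health outcomes.

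**Working it through.** **1. Inputs from the protocol.** Sessions: 18 weeks × 2 = 36 (section 2.6). Threshold: 0.75 × 36 = 27 sessions (section 2.4). Training-group size: 26 (section 2.3). The article states no expected attendance, so there is no planned figure to reproduce.

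**2. When the criterion acts.** Randomization precedes every session, so (h) can remove only people already randomised, and only from the training group.

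**3. Floor on attendance, if (h) defines the feasibility set.** Each person counted has attended at least 27/36 = 75%, so the mean cannot be lower. Over all 26 randomised there is no such floor.

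**4. Effect on retention, under the same condition.** Each fully assessed but excluded member lowers training-group retention by 1/26 = 3.8 points.

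Illustration with assumed values: k of the 26 fall below 75% and average 30% to 50% attendance, the others average 90%, and all 26 complete every assessment. Mean attendance over all randomised is [(26 − k) × 0.90 + k × low] / 26.

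| k | Attendance, all randomised | Attendance after (h) | Retention by assessments completed | Retention if excluded count as lost |
|---|---|---|---|---|
| 4 | 81% to 84% | 90% | 100% | 22/26 = 84.6% |
| 8 | 72% to 78% | 90% | 100% | 18/26 = 69.2% |

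For example, with k = 8 and low = 0.30: (18 × 0.90 + 8 × 0.30)/26 = 18.6/26 = 71.5%.

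**5. Size of the attendance inflation.** The attendance distribution is unknown, so it is assumed. Each person's attendance probability follows a beta distribution with mean m and SD s, and sessions attended are binomial over 36. The beta parameters are m·c and (1 − m)·c, with c = m(1 − m)/s² − 1. For m = 0.70 and s = 0.20, c = 0.21/0.04 − 1 = 4.25, giving parameters 2.975 and 1.275. The reported mean is the expected share of sessions attended among those with at least 27.

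| True mean | Reported, SD 0.15 | Removed | Reported, SD 0.20 | Removed |
|---|---|---|---|---|
| 60% | 82% | 77% | 84% | 70% |
| 70% | 84% | 54% | 87% | 50% |
| 80% | 89% | 30% | 92% | 30% |
| 85% | 92% | 20% | 94% | 22% |
| 90% | 95% | 13% | 97% | 14% |

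At true means of 85–90% the inflation is about 5 to 9 points. Programmes with true attendance of 60% and 80% would be reported only about 7 points apart.

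**The case against.** A reader might infer that reported attendance cannot fall below 75%, or that the protocol counts fully assessed low attenders as lost. The document does not say either. Section 2.10 names no analysis set and leaves retention undefined, and section 2.6 records attendance session by session, so a calculation over everyone randomised is open to the investigators. The adherence adjustment in section 2.9 also suggests that low attenders stay in the data. The Figure 1 note is weak evidence: the diagram is not shown, and the note may only explain projected numbers. This part of the objection stands, and it is why the point is conditional.

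It can also be said that denominators for descriptive indicators are the kind of detail an article leaves to a fuller document. That would be decisive if the article were merely silent. It is not silent: the one rule it states about low attenders is that they are excluded. The intention-to-treat sentence does not override that rule here, because it covers group comparisons, and attendance and adherence are descriptive figures from one arm.

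It would also go too far to say that a poorly attended programme would pass unnoticed. If excluded members count as lost, a true mean of 60% would leave training-group retention of at most about 23–30%. The failure would show, but under the label of retention.

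Finally, true means of 60–80% remove 30% or more of the arm, whereas section 2.3 allows for 15% dropout. At 85–90% the distortion is smaller, though not negligible.

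**Conclusion.** The point holds in conditional form. Criterion (h) is a post-randomization exclusion in one arm, based on a variable that section 2.10 reports as a result. If it is applied as written to the feasibility set, mean attendance is at least 75% by construction, and each fully assessed low attender costs the training group 3.8 points of retention, with no counterpart in the control group. No statement in the article rules this out.

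The 75% floor and the 3.8 points follow from the protocol's own numbers once that condition is met. The inflation figures rest on an assumed beta-binomial distribution with SD 0.15 to 0.20: 70% becomes 84–87%, 80% becomes 89–92%, and 90% becomes 95–97%. Because feasibility is half of the stated aim and the correction is cheap, the change should be made.

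**What to change.** 1. In section 2.4, stop treating (h) as an exclusion from the study. Confine it to a per-protocol sensitivity set, which also brings it into line with the intention-to-treat principle in section 2.9.
2. In section 2.10, state that attendance and adherence are computed over all participants randomised to the training group, with 36 supervised sessions as the attendance denominator and non-starters counted as zero.
3. Define retention in each arm as the share of randomised participants who complete each assessment, whatever their attendance.
4. Report the share of the training group reaching 75% attendance as a feasibility result in its own right.

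The cost is a few sentences. Attendance is already to be recorded at every session, and the intervention had not begun when the article was written. Low attenders would need to be kept in follow-up and invited to every assessment. The downside is that the feasibility figures may look less favourable.

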## 3. Discussion

The objective of the current protocol will be to determine the feasibility and evaluate the effects of a preliminary outdoor multidomain intervention (ACTIVA-Senior program) for 18 weeks, twice per week, through a randomized controlled trial on cognitive state, body composition, sarcopenia, cardiovascular health, physical fitness, emotional state, frailty, satisfaction with life, and motivation in late middle-aged and older adults. According to the WHO [75], the period from 2020 to 2030 is designated as the “Decade of Healthy Aging”, with a key objective of promoting equality and equity of opportunities for individuals to enjoy the benefits of determinants and facilitators of healthy aging, regardless of age, sex, place of birth or residence, immigration status, or skill level. This project aligns with the “Health, demographic change, and well-being” challenge, as it aims to understand the effects of multimodal interventions on the health of older adults and to educate them on adopting a healthy lifestyle for improved quality of life [5,13]. Furthermore, by including individuals from the age of 55, this protocol emphasizes the preventive dimension of the intervention, recognizing that early engagement in multidomain training may help delay the onset of frailty and cognitive decline and support healthier aging trajectories.

The direct impact of the ACTIVA-Senior study is based on evidence demonstrating the benefits of physical exercise together with cognitive tasks in the prevention and improvement of chronic diseases among late middle-aged and older adults, educating them on adopting active aging and healthy habits, including regular participation in an appropriate physical exercise program [17,18,31]. The inclusion of feasibility and acceptability outcomes provides valuable insights into the practical implementation of the ACTIVA-Senior program, which are essential for refining the intervention and designing future larger trials.

In Spain, over half of the middle-aged and older population is affected by overweightness and chronic diseases [1]. Increased engagement in physical exercise and adoption of healthy habits can lead to a 10% reduction in healthcare expenses, with every euro invested in exercise potentially saving six euros in healthcare costs [76]. Moreover, establishing a holistic and sustainable program aimed at promoting community health is vital for combating dementia and reducing dependency [77]. These findings justify the need for non-pharmacological intervention projects that investigate the effects of multidomain training programs on health in middle-aged and older adults.

However, this study has some limitations. First, conducting a randomized controlled trial aimed at modifying healthy habits and physical activity presents challenges related to participant adherence, retention, and expectancy effects. The absence of an active control group, such as a group that participates in a health education program or other types of training, may influence behavioral and quality-of-life outcomes. However, the objective in establishing this no-treatment control group will be to obtain a realistic picture of how these variables evolve without any intervention, which is usually the case in this population. In future studies, it would be necessary to incorporate such components to improve engagement, better control for expectancy, and enhance interpretability. Second, while validated questionnaires and objective tests are employed, self-reported data remain susceptible to recall and social desirability biases. Third, although the sample size was informed by effect sizes from previous multidomain interventions, the relatively small cohort may limit generalizability and increase the risk of Type II errors. Finally, given the inclusion of a healthy population and the absence of cognitive screening upon recruitment, there is a potential for a ceiling effect in cognitive outcomes, which should be considered when interpreting future results. As such, findings will have to be interpreted with caution and viewed as preliminary pending confirmation in larger trials.

## 4. Conclusions

This preliminary study protocol outlines a randomized controlled trial designed to evaluate the efficacy and feasibility of a multidomain intervention, delivered entirely outdoors, which incorporates physical exercise and cognitive tasks aimed at promoting healthy aging and mitigating psycho-physiological decline. These approaches not only enhance the quality of life for older adults living independently but also have the potential to reduce healthcare costs by encouraging healthier aging in late middle-aged adults. This study’s findings are expected to shed light on a promising avenue for improving adherence among middle-aged and older adults, especially in outdoor multidomain interventions, an area that warrants further exploration.

## Figures and Tables

**Figure 1 healthcare-13-01110-f001:**
[figure not shown]
Consolidated Standards of Reporting Trials flow diagram showing the flow of participants through each stage of the study. NOTE: The follow-up accounts for potential participant exclusion based on expected attrition observed in previous studies.

**Table 1 healthcare-13-01110-t001:** SPIRIT schedule of enrolment, interventions, and assessments.

Study Period	Enrolment	Pre-Intervention (Pre-Test)	Familiarization (2 Weeks)	Intervention (Weeks 1–18)	Post-Intervention (Post-Test)	3-Month Follow-Up (Re-Test 1)	6-Month Follow-Up (Re-Test 2)
Informed Consent	X						
Eligibility Screening	X						
Randomization	X						
Baseline Assessments		X					
Multidomain Intervention			X	X			
Outcome Assessments					X	X	X

**Table 2 healthcare-13-01110-t002:** Distribution of content between the weekly sessions.

Session Part	Content	Details	Monitoring	Cognitive Integration
Warm-up (10 min)	- Activation exercises - Joint mobility	Playful tasks and movement prep activities; progressive cardiorespiratory stimulus.	RPE (Borg), trainer supervision	Sensorimotor activities, coordination-based games
Main (40 min)	First weekly session Local muscle endurance (1) Balance and coordination	Circuit of 8 exercises (6 strength, 2 balance/coordination). 3–4 sets of 10–12 reps. 20–30 s rest between exercises. Equipment: dumbbells, bands, TRX.	OMNI-RES RPE (6–7/10), trainer diary	Dual tasks (e.g., movement + verbal/cognitive tasks)
	Second weekly session Power training + local muscle endurance (2) Cardiorespiratory	Power block: 3 exercises, 2 sets of 6–8 reps. Load moved as fast as possible. Local muscle endurance block: 3 exercises, 3 sets of 10–12 reps. Cardio: 2 × 4 min intervals, moderate to vigorous using the talk test.	OMNI-RES RPE, Borg scale, trainer diary	Dual tasks, attention/memory components
Cool-down (10 min)	- Flexibility - Relaxation - Emotional intelligence tasks	Static stretching (8 exercises, 10–30 s), body–mind exercises (Tai Chi, breathing), emotional intelligence games (collaboration, expression of feelings).	Trainer checklist	Breathing visualization, reflective and emotional tasks
Autonomous training	Brisk walking (2×/week)	30+ min per session, moderate intensity. Monitored via self-reported training diaries and talk test.	Training diary (duration, distance, RPE)	—

**Table 3 healthcare-13-01110-t003:** Description of outcome measures.

	Dimension	Test	Description
Primary evaluations	Sociodemographic questionnaire	Ad hoc	An ad hoc questionnaire used in previous research [1] will be used to collect data on age, sex, physical independence, history of chronic diseases, and systematic exercise.
	Cognitive state	Victoria Stroop Test (VST)	The Stroop test assesses attention, inhibition, and processing speed, observing the Stroop effect where reading interferes with color identification. The test involves three phases and aims to distinguish between colors and words accurately without errors [2].
		Trail Making Test (TMT)	TMT test assesses thought flexibility and visuospatial ability. It involves connecting numbers and words in a numerical sequence without making errors.
	Body composition and anthropometric variables	Bioimpedance + Anthropometry variables + Proportionality variables	Regarding body composition, fat mass, fat-free mass, lean mass, and muscle mass will be assessed with Inbody 120. The measurements shall be carried out according to the manufacturer’s standardization conditions and previous studies [3]. Body mass, with Inbody 120; height with SECA 217 scale; and waist and hips with Lufkin tape; will be assessed according to the guidelines of the International Society for the Advancement of Anthropometry (ISAK) [4]. Subsequently, BMI (kg/m^2^), as well as waist/hip and waist/height ratio, will be calculated [5]
	Sarcopenia	Handgrip test and chair stand test (CST) (5-times sit-to-stand)	The probability of sarcopenia will be assessed using the handgrip test with a Takei tkk5401 dynamometer (P & A Medical Ltd., Duxbury, UK) and CST (5 times sit-to-stand), following the indications of the European consensus on definition and diagnosis [6]. The tests will be performed according to the protocol of previous research [7].
		Muscle mass	For the diagnosis of sarcopenia, muscle mass will be assessed using Inbody 120, following the indications of the European consensus on definition and diagnosis [6]. The tests will be performed according to the protocol of previous research [3].
		Timed Up and Go test (TUG) + Gait speed test (4 m walk test—4MWT) + Short Physical Performance Battery (SPPB)	The severity of sarcopenia (functional performance) will be assessed using TUG, gait speed, and the SPPB test, following the indications of the European consensus on definition and diagnosis [6]. The tests will be performed according to the protocol of previous research [7]. Photovoltaic cells from Microgate (Bolzano, Italy) will be used for TUG and 4MWT. The SPPB battery includes the balance test, gait speed test, and chair stand test. The Total SPPB score, ranging from 0 to 12, will be calculated by adding the scores from the three individual tests, following previous studies [8].
	Cardiovascular state	Blood pressure and resting heart rate	Blood pressure and resting heart rate will be measured using a calibrated and automated device (Omron M6W, Omron Healthcare Ltd. Hoffman Estates, IL, USA), following the protocol of previous studies [9]
	Physical fitness	Upper and lower limbs muscle strength	Upper and lower limb isometric muscle strength will be evaluated using the functional electromechanical dynamometer Dinasystem. For this purpose, the following exercises will be performed randomly, maintaining the isometric phase for 6 s during evaluation: bilateral rowing; bilateral push from the seated position with shoulder abduction at 45° and elbow flexion at 90°; and the sit-to-stand test. All of this will follow the methodology of previous research [10].
		Velocity	The 10 m walk test (10MWT) will be used for the assessment of velocity. Photovoltaic cells from Microgate (Bolzano, Italy) will be used for evaluation. This test will be conducted following the guidelines of previous research [11].
		Cardiorespiratory fitness	The 6-minute walk test will be used for the assessment of cardiorespiratory fitness. The distance covered, heart rate at the end, and heart rate recovery at 1 and 3 min will be recorded, following previous studies [12].
		Flexibility	Sit-and-reach test with a box (Acuflex, Psymtec, Madrid, Spain) and back scratch test will be used for the assessment of flexibility, following the protocol of previous studies [13]
Secondary evaluations	Physical activity (PA)	International Physical Activity Questionnaire (IPAQ-SF)	The short version of the IPAQ-SF for adults will be used to analyze levels of PA [14]
	Frailty	Fried questionnaire	The Fried questionnaire evaluates five criteria related to frailty: involuntary weight loss, exhaustion, weakness, slow gait speed, and low physical activity. The number of criteria met is classified as a three-level variable representing robustness (0 criteria met), pre-frailty (1 or 2 criteria met), and frailty (3 or more criteria met) [15].
	Emotional state	Centre for Epidemiological Studies Depression Scale-Revised (CESD-R)	The CESD-R is a 20-item questionnaire that measures depressive symptoms among older participants. Participants indicate the number of days on which they experienced depressive symptoms during the previous week using a standard four-point Likert scale. Higher scores indicate more depressive symptoms [16].
		Perceived Stress Questionnaire (PSQ)	The Perceived Stress Questionnaire (PSQ) is a psychological tool used to assess an individual’s subjective perception of stress in their daily life, focusing on feelings, thoughts, and reactions to stressful situations [17].
		Emotional intelligence in adults (EQ-i-M20)	The EQ-i-M20 is a 20-item questionnaire with subcategories such as intrapersonal, interpersonal, stress management, adaptability, and general mood [18].
	Satisfaction with life	Satisfaction with Life Scale (SWL)	The scale consists of four items rated on a Likert-type scale, ranging from 1 to 7, which assesses global subjective happiness [19].
	(e) Motivation	Behavioral Regulation during Exercise Questionnaire-3 (BREQ-3)	The BREQ-3 will be used to assess motivational regulation related to physical exercise. The questionnaire consists of twenty-three items distributed across three dimensions based on the Self-Determination Theory (SDT), which distinguishes between autonomous motivation, controlled motivation, and amotivation [20].

